##### D. Visit 10 (D35±3)

1. Participant dropouts

Calculate treatment adherence for participants.

Example) Treatment Adherence (%) = Participant's actual acupuncture treatments / 10 acupuncture treatments

Adherence to acupuncture treatment: □□.□ %

1. Vital signs and weight measurement

Measure and record vital signs and weight.

For vital signs, check and record body temperature, systolic blood pressure, diastolic blood pressure, and pulse rate.

1. Verify conditions/medications/treatments (check for changes in medical history and medication adherence)

Check for any new conditions, additional medications, or other treatments since visit 9. If so, record in the Condition/Medications/Treatments CRF form

1. General physical exam

Determine if the particiapant has any of the conditions listed on the general physical examination form in the CRF at the time of the visit. If present, circle yes and record in the abnormal findings section below.

V for none.

1. Acupuncture or electroacupuncture

A researcher who did not participate in the survey will administer the appropriate treatment to the randomized acupuncture or electroacupuncture arm.

1. Thermometer measurements

Before and after treatment, bilateral temperatures at the anterior thigh (ST32) and dorsum of the foot (LR3), and palm (PC8) and arm (LU4) will be measured using a non-contact infrared thermometer at a distance of 3cm for three consecutive readings, and the median value excluding the highest and lowest values will be recorded.

1. Visual Analogue Scale (VAS) of coldhypersensitivity in the hands and feet

The VAS of coldhypersensitivity in the hands and feet will be completed by the participant with the assistance of the researcher. On the VAS, participants will mark an I for their level of hands and feet coldness.

O, V, not verbalized (to be precise)

1. Screening for and identifying adverse events

Check for any adverse events that occurred during the study. If so, create an adverse event report in the CRF.

Adverse event reporting procedures are in accordance with the adverse event reporting SOP and the standard operating procedures for acupuncture treatment administration.

1. The Korean version of the World Health Organization Quality of Life Scale (Short Form) (WHOQOL-BREF) and the EQ-5D Quality of Life Assessment

Use ◯ only for the most appropriate number.

In the paper medical record, keep the questionnaire and, if it is an electronic medical record, record the score, description, or item number. If this is difficult, create and store a paper medical record file for your study.

1. Coldness Diagnostic Questionnaire

Let the participant fill in the fields that need to be filled in.

The measurement must be performed by a practitioner.

1. Laboratory tests

General hematology tests for WBC, RBC, Hemoglobin, and Platelets.

Blood chemistry tests for BUN, Creatinine, AST, ALT, and r-GTP.

It will be performed in the laboratory of each participating medical center.

The korean medical hospital will refer the above tests to the laboratory of a western medical institution for testing.

1. Specify your next visit date

Remind participants to schedule their next visit within 4 weeks ± 7 days.

##### E. Visit 11 (D63±7)

1. Vital signs and weight measurement

Measure and record vital signs and weight.

For vital signs, check and record body temperature, systolic blood pressure, diastolic blood pressure, and pulse rate.

1. Verify conditions/medications/treatments (check for changes in medical history and medication adherence)

Check for any new medical conditions, additional medications, or other treatments during the period from Visit 10 to Visit 11.

If so, record it in the Condition/Medical Supplies/Treatment CRF form.

1. General physical exam

Determine if the participant has any of the conditions listed on the general physical examination form in the CRF at the time of the visit. If present, circle yes and record in the abnormal findings section below.

V for none.

1. Thermometer measurements

At each visit, bilateral temperatures at the anterior thigh (ST32) and dorsum of the foot (LR3), and palm (PC8) and arm (LU4) will be measured using a non-contact infrared thermometer at a distance of 3cm for three consecutive readings, and the median value excluding the highest and lowest readings will be recorded.

1. Visual Analogue Scale (VAS) of coldhypersensitivity in the hands and feet

The VAS of coldhypersensitivity in the hands and feet will be completed by the participant with the assistance of the researcher. On the VAS, participants will mark an I for their level of hands and feet coldness.

O, V, not verbalized (to be precise)

1. Screening for and identifying adverse events

Check for any adverse events that occurred during the four weeks. If there are any, create an adverse event report in the CRF.

Adverse event reporting procedures are in accordance with the adverse event reporting SOP and the standard operating procedures for acupuncture treatment administration.

1. The Korean version of the World Health Organization Quality of Life Scale (Short Form) (WHOQOL-BREF) and the EQ-5D Quality of Life Assessment

Check ◯ only for the most appropriate number.

In the paper medical record, keep the questionnaire and, if it is an electronic medical record, record the score, description, or item number. If this is difficult, create and store a paper medical record file for your study.

1. Coldness Diagnostic Questionnaire

Let the participant fill in the fields that need to be filled in. The measurement must be performed by a practitioner.

##### F. End of Study

1. V for Yes if the trial is finalized and record the end date.

Example) Was the trial completed in accordance with the protocol?

□ Yes → End date 20□□Year □□Month □□Day

1. If you dropped out of the study midway through or lost compliance, V-Check No in the CRF form [Study Terminated], complete the date of the dropout or withdrawal, and V-Check the reason for the dropout or withdrawal.

Example) □ No → Suspension or dropout date20□□Year □□Month □□Day

Causes of study discontinuation or dropout

- - Violation of Inclusion/Exclusion Criteria
  - Unidentified systemic disease before clinical trial
  - Adverse reaction
  - Intercurrent illness (not intervention related)
  - Participant's request for withdrawal (other than adverse reaction)
  - Investigator indicated termination
  - Exclusion from study due to non-adherence to protocol
  - Pursuit failure
  - Other other ( )

1. Make any notes in the progress or overall comments.
2. The principal investigator must sign and date the CRF after finalizing it.

##### G. Complete CRF and finalize case closure signature

1. Once the CRF is finalized, the principal investigator checks that it matches the supporting documentation (medical records) and identifies any discrepancies, missing records, or missing CRF checks.
2. Check for omissions through monitoring, etc.
3. Verify that the supporting documentation matches the CRF and that the consent form is signed, dated, and signed with no misspellings.
4. The investigator and principal investigator finalize the completion of the CRF by signing the case conclusion to assure compliance with the case record.

#### Predicted Adverse Events and Precautions for Use of Acupuncture

##### Predicted adverse events

Acupuncture and electroacupuncture are generally considered to have the potential to cause adverse reactions, including redness, swelling, edema, pain, and purpura, based on what is known to occur.

##### Precautions for use

Precautions for acupuncture and electroacupuncture include below

Pay attention to hygiene when storing acupuncture treatments

Be mindful of hygiene and infection when needling

Stop if patient complains of severe pain

#### Study discontinued, study participants Exclusion Criteria

Particiapants will be excluded from the study if any of the following conditions apply, as determined by researcher.

##### Particiapants will be dropped from the study if the predicted treatment adherence is less than 70% at the end of the study. Failure to visit within ±3 days of the scheduled visit will be considered a missed visit.

##### Became pregnant during the study

##### If surgery or hospitalization is required due to a disaster such as an accident or the onset of other diseases

##### In case of refusal by a clinical trial participant

##### Prohibited concomitant medications and therapies.

Example) Anticoagulants, psychotropic medications, antidepressants, medications related to hyperthyroidism, dietary supplements (such as red ginseng), OTC blood flow enhancers, and other medications that may affect coldhypersensitivity in the hands and feet.

##### Worsening of coldhypersensitivity in the hands or feet requiring standard treatment.

##### Serious adverse events that make it unreasonable to continue in the study.

##### Other unavoidable reasons have arisen that make it impossible to continue the study or that the principal investigator believes would have affected the outcome of the study.

For those who drop out, we will recommend conventional medical treatment of coldhypersensitivity in the hands and feet if the participant wants additional treatment, or standardized treatment if the participant wants maintenance treatment. The duration of treatment for these dropped particiapnts and the issue of compensation with or without treatment will be determined by the institutional review board according to the condition of the dropped participants and the causal relationship with acupuncture treatment.

#### Criteria for evaluating safety, how it is evaluated, and how it is reported to

##### Predictable or Unpredictable Adverse Events

An adverse event is an undesirable, unintended event, symptom, or illness that occurs during the course of a clinical trial and is not necessarily causally related to the intervention.

Predictable adverse events

The types of adverse reactions that can occur with body or electroacupuncture include below

- Localized abnormalities

Subcutaneous hemorrhage and hemorrhagic bullae formation

Peripheral neuritis/ Cellulitis

Localized tingling sensation

Allergic reaction to needle cramps or burning needles

Pain at the needle site (only if it lasts longer than 2 weeks)

- Autonomic and central nervous system abnormalities

Drop in blood pressure and fainting/excessive sweating Drowsiness (only if lasting more than 1 week)

Confusion (only if lasting more than 1 day) / Coma

- Gastrointestinal abnormalities Nausea/vomiting
- Mental issues

Anxiety, fear (only if it lasts for more than 60 hours per incident) Drowsiness

- Other

Headache (only if it lasts more than 3 days)

Hypersensitivity with tingling symptoms (only if lasting more than 3 days)

Attacks after needle insertion

Unclear language

Unpredictable adverse events

A discrepancy in the modality or degree of harm in light of available information about body acupuncture and electroacupuncture (e.g., acupuncture practice guidelines, acupuncture textbooks, relevant literature).

Cautions for use

If a participant complains of excessive fatigue or declining health on the day of a scheduled acupuncture or electroacupuncture treatment, or if the study researcher examines the participant via diagnosis and determines that the participant's condition is not suitable for treatment, the treatment date can be rescheduled within 3 days before or after the scheduled date to avoid potential adverse events associated with treatment.

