##### D. Observe adverse events

Participants are trained to voluntarily report information about any adverse events that occurred during the study period, and the investigators verify the presence of adverse events through laboratory tests and questionnaires.

The investigator should evaluate adverse events and record any previously unrecorded adverse events in the appropriate section of the case record, indicating the action taken, the nature of the event, date and time of onset, duration, severity, and relation to acupuncture or electroacupuncture. Any changes in the frequency or severity of adverse events during the study should be recorded on a separate page.

1. Assessing the severity of an adverse event

Based on clinical signs and symptoms of an adverse event, the criteria are as follows

| 1 = Mild | Does not interfere with normal daily life (functioning) to the extent that it is barely noticeable to the study participant.  Mostly not requiring treatment. |
| --- | --- |
| 2 = Moderate | The degree to which the participant is uncomfortable and interferes with normal daily activities (functioning).  The degree to which the particiapant may be able to continue the study but may need treatment. |
| 3 = Severe | The degree to which the participant is so uncomfortable that daily activities (functioning) are not possible and continued participation in the study is not possible.  The extent to which treatment or hospitalization may be required |

1. Evaluating acupuncture and causality

The degree of certainty that an adverse event can be attributed to acupuncture or electroacupuncture (or to other causes, such as the natural history of the underlying condition or concomitant therapies) is determined by how well the adverse event fits the following criteria: the adverse event appeared after starting acupuncture, disappeared after discontinuation, or reappeared upon reuse, indicating that it is related to acupuncture treatment.

1 = Definitely relevant Certain > 90%

2 = Highly relevant Probable/likely > 70%

3 = Possibly related Possible 50%

4 = Not thought to be relevant Unlikely < 30%

5 = Difficult to determine relevance Conditional/ unclassified < 10%

1. Serious adverse events

"Serious adverse event" means an event that meets 1 of the following criteria

A) Causes death or is life-threatening;

B) Requires hospitalization or extended hospitalization.

C) Causes persistent or significant disfigurement or impairment

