**E. Reporting**

The principal investigator will educate co-investigators and participants about any adverse reactions that may occur after acupuncture or electroacupuncture interventions and will educate them to report any phenomena that occur after the intervention.

All systemic or pathologic symptoms that occur after acupuncture or electroacupuncture interventions shall be recorded and kept in a case record sheet that conforms to the standards of clinical trial management, including the type, time of occurrence, severity, treatment, therapeutic agent, outcome, and causal relationship to acupuncture treatment.

If a "serious adverse event" occurs during the study, it will be reported to the Institutional Review Board (IRB) to determine whether the study should be continued or discontinued.

1. If participants die during the study or pose a serious risk to life, this will be reported within 7 days of receiving the report, but in this case, further details will be reported within 8 days of the initial report.
2. For all other serious and unexpected adverse events, report them within 15 days of the date the sponsor is informed or becomes aware of them.
3. Additional safety information related to the reporting of the above should be reported by phone or in-person by the investigator until 7 days after the end of the study (washout period).
4. The principal investigator shall conduct all aspects of the study in accordance with the Declaration of Helsinki.

□ Women of childbearing age

①Women of childbearing potential must have a negative urine pregnancy test prior to study entry.

②Women of childbearing potential must be using adequate and reliable contraception for at least 1 month prior to study entry and continue for the duration of the study.

③If you think you may become pregnant during the study, notify the study staff immediately, and the pregnancy test may be repeated.

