##### Analysis of safety endpoints

- - 1. Clinical laboratory test data will be analysed using appropriate statistical methods, including within-group comparisons before and after treatment, depending on the nature of the variable, and the frequency, incidence, list, detailed time of occurrence, severity, and causal relationship to acupuncture treatment will be reported in graphical form, if necessary. The statistical analysis will be performed by ANOVA, t-test, chi-square or Fisher's exact test, depending on the nature of the variable.
    2. Adverse events: Table all adverse events, categorized by treatment group and body system, with detailed descriptions. For each group, record the frequency of adverse events that are causally related to acupuncture treatment and those that are not causally related. Determine the number of AEs and the proportion of participants experiencing at least one AE within each arm with 95% confidence intervals and compare between arms.
    3. Clinical pathology: Descriptive statistics will be presented for each group and visit for continuous data such as hematology and blood biochemistry test results and vital signs, and differences between visits will be analysed using paired t-test or non-parametric methods.

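### The protocol defines adverse events without a minimum duration but lists six predictable reactions only if they last from over 1 day to over 2 weeks, and its causality scale ranks undeterminable events below unlikely ones

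*Protocol*

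**What the plan says.** Five places in the protocol bear on this.

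- **Predictable or Unpredictable Adverse Events**, definition: "An adverse event is an undesirable, unintended event, symptom, or illness that occurs during the course of a clinical trial". It sets no minimum duration.
- **The same section**, list of predictable reactions: six entries carry a duration condition. Examples are "Pain at the needle site (only if it lasts longer than 2 weeks", "Drowsiness (only if lasting more than 1 week" and "Anxiety, fear (only if it lasts for more than 60 hours per incident) Drowsiness". In the last of these, drowsiness is listed again, this time with no limit.
- **Predicted adverse events**: the reactions known for acupuncture and electroacupuncture are given as "including redness, swelling, edema, pain, and purpura, based on what is known to occur". Pain has no limit here.
- **E. Reporting**: "All systemic or pathologic symptoms that occur after acupuncture or electroacupuncture interventions shall be recorded".
- **Analysis of safety endpoints**: all adverse events are tabulated by group and body system. The proportion of participants with at least one is given with a 95% confidence interval and compared between arms. For each group the plan is also to "record the frequency of adverse events that are causally related to acupuncture treatment and those that are not causally related".

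On causality, **D. Observe adverse events** gives a five-grade scale with percentages. Grade 4 (unlikely) is set at below 30%. Grade 5 reads "5 = Difficult to determine relevance Conditional/ unclassified < 10" percent.

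**The concern.** Safety is in the trial's title and objective, and the planned safety result is a between-arm comparison of adverse event proportions. That result is only as good as the rule for what enters the case report form. A site that takes the duration conditions literally would leave out needle-site pain lasting ten days. A site that follows the reporting section would enter it. Needle-site pain can arise only in the two needled arms, so leaving it out would bear on one side of the comparison with no treatment. An event that was never recorded cannot be recovered at analysis.

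The causality scale raises a second, smaller problem. Not being able to judge causality is different from judging it improbable. The scale gives the undeterminable grade the lowest percentage, which invites whoever makes the related/not related split to count those events as unrelated.

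**Working it through.** The protocol states no adverse event rate, so there is no figure to reproduce. The check is a comparison of texts, a count and one conditional illustration.

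**1. Duration conditions in the list of predictable reactions**

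| Reaction | Listed only if it lasts more than |
|---|---|
| Needle-site pain | 2 weeks |
| Drowsiness (autonomic and central nervous system group) | 1 week |
| Headache | 3 days |
| Hypersensitivity with tingling | 3 days |
| Anxiety, fear | 60 hours |
| Confusion | 1 day |

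Counting the list entries gives about 17, depending on how combined entries are split. Six carry a limit and 17 − 6 = 11 do not. Those without one include subcutaneous hemorrhage, localized tingling, allergic reaction, fainting and nausea.

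**2. Against the other sections**

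- The definition at the head of the same section has no duration floor, so a two-day headache meets the definition but not the list.
- Predicted adverse events names pain without a limit; the later list limits needle-site pain to more than 2 weeks.
- E. Reporting covers all symptoms after the intervention; the list, read as a filter, does not.
- D. Observe adverse events already requires duration to be recorded and has a mild grade for barely noticeable events. A floor of up to 2 weeks sits badly with both.
- Drowsiness is both limited and unlimited within one list.

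**3. What the 2-week limit means on this schedule**

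Treatment is twice a week for 5 weeks. Two weeks × 2 sessions = 4 of the 10 sessions. Pain that resolves before the next session would never meet the condition.

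**4. Illustration, conditional on assumed rates**

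Assume that the limit is used as a recording filter. There are 24 + 24 = 48 needled participants. Let p be the assumed risk of any needle-site pain and f the assumed share of those cases lasting more than 2 weeks.

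With pain = 48 × p; counted under the limit = 48 × p × f.

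| p | With pain | Counted, f = 5% | Counted, f = 20% |
|---|---|---|---|
| 10% | 4.8 | 0.24 | 0.96 |
| 20% | 9.6 | 0.48 | 1.92 |
| 40% | 19.2 | 0.96 | 3.84 |

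These are counts of needle-site pain only. They are not the planned proportion with at least one event of any kind, because a participant who also has, say, bruising would still be counted.

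**5. Causality scale**

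The percentages run above 90, above 70, 50, below 30 and below 10. The last belongs to the grade for events that are difficult to determine, and the one before it to unlikely events. An event about which nothing can be said is therefore placed lower on relatedness than one judged unlikely. The analysis section needs a two-way split but does not say which grades fall on which side.

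**The case against.** The strongest reply is that the durations are not a recording rule at all. They stand in a list of predictable reactions, set against unpredictable ones, and so may describe expectedness only. Every operative instruction points to full recording: the definition, the visit-by-visit instruction to check for any adverse event, the duration field, the reporting section and the tabulation of all events. This stands to the extent that the protocol nowhere says a shorter event is not an adverse event. It does not clear the contradiction. On the expectedness reading, needle-site pain of two days would not be predictable while pain of three weeks would be. Yet the same section defines unpredictable as a departure in type or degree from known harms, and pain is predicted elsewhere without a limit. A site could reasonably read the wording either way.

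A reader might infer that expected needling harms in general count only if they last days to weeks. The list does not support that: 11 of about 17 entries have no limit, and localized tingling and subcutaneous hemorrhage are among them. Headache, drowsiness, anxiety and confusion can also occur without needling, and adverse events are checked in all three groups at Visits 10 and 11, so a filter on those would not act on the treated arms alone.

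A reader might also infer that undeterminable events will be classed as unrelated. The protocol sets no cut-off, and a statistical analysis plan could supply one. Whatever the split, such events stay in the table of all adverse events and in the proportion with at least one. What remains is that any cut-off would be applied to a mis-ordered scale, and that error is in the protocol's own text. The jumps between percentage bands and the lack of a grade named not related are weaker points: the 50% entry is a bare figure in a translated list, and grade 4 already serves roughly as not related. Neither is relied on here.

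**Conclusion.** The point holds as a contradiction to be reconciled and a defect in the causality scale. It does not hold as a finding that the safety endpoint understates harm. Six listed reactions carry limits from more than 1 day to more than 2 weeks, in conflict with the definition, with the unlimited entry for pain, with the duty to record all symptoms and with the second entry for drowsiness. Understatement would follow only if sites used the limits as a filter, or, for the count of related events, if the undeterminable grade were classed as unrelated; the documents establish neither. Differing practice across the three sites is likewise a risk created by the wording and not a demonstrated fact. The illustrative counts rest wholly on assumed risks and durations. The change is worth making before recruitment because unrecorded events are lost for good.

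**What to change.** - In Predictable or Unpredictable Adverse Events, remove the durations as a condition for recording, or state that they bear only on expectedness. Say that every event meeting the definition is recorded whatever its duration, using the duration field already required under D. Observe adverse events.
- Make that section agree with Predicted adverse events, E. Reporting and Analysis of safety endpoints, and resolve the double entry for drowsiness.
- Take the undeterminable grade out of the percentage order and label it not assessable. Tabulate it separately, or state in advance how it enters the related/not related split. Counting it as related is one conservative convention, but any rule fixed in advance would do.
- State which of the remaining grades count as related.

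The cost is a change of protocol and case report form wording and more entries for mild events. Reported adverse event rates in the treated arms will probably be higher than under a filter.
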